#### Secondary outcomes

Secondary outcomes include: 1) number of times in past 3 months had sex without a condom, 2) number of times in past 3 months had sex without birth control, 3) number of partners in past 3 months, 4) number of new partners in past 3 months, 5) current symptoms of STI, 6) alcohol and drug use in past 3 months, 7) alcohol and drug use before sex in past 3 months, 8) condom use self-efficacy, 9) condom use intention, 10) attitudes towards condom use, 11) belief condoms prevent STI/pregnancy,12) birth control intention, 13) STI screening intention, 14) sexual health knowledge, 15) connectedness to school, 16) use of time in sports/recreational/religious activities, 17) family communication, 18) peer role model/influence, 19) healthy peer norms, and 20) aspirations for the future.

### Statistical analysis

Study hypotheses will be tested using an “intent to treat” analysis. Baseline characteristics will be compared between groups using chi-square tests for binary or categorical outcomes, and Wilcoxon rank-sum tests for continuous outcomes. For the primary outcome of STI screening uptake, the proportion of participants completing screening (i.e. returning a test to study staff) by the 3-month study visit will be compared across groups using a chi-square test or log-binomial regression if participant characteristics are found to vary at baseline between groups. For all analyses, participants who drop-out during the study and don’t provide at least 3-month follow-up data will be removed from the analysis. If at 3- or 6-months follow-up the POFG intervention shows efficacy for increasing STI screening uptake, we will conduct mediation and moderation analyses to explore what factors may be impacting the efficacy of POFG to change STI screening behavior.

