### Participant randomization and study sample size

This study is at RCT. The randomization sequence is computer generated and used to randomize individuals to one of two study groups: intervention or control. A stratified randomization technique will be used to ensure equivalent 1:1 allocation of study conditions across three gender groups (male/trans male; female/trans female and other, which includes those who identify as two-spirited, bi-gendered, crossdresser, genderqueer, or for whom none of these options apply), and three age groups (i.e. 14–17, 18–21, and 22–26). Within each age/gender strata, participants will be randomized in blocks of 4 to ensure equal allocation to intervention and control groups. Participants, but not study staff or investigators, will be blinded to study group participation.

The primary outcome is completion of self-administered STI screening between the baseline and 3-month study visit. Based on prior research, we estimate that 20–25% of the control group will complete STI screening [12]. We anticipate POFG will increase STI screening by at least 50% (i.e. relative risk of 1.5 comparing the proportion completing STI screening in the intervention group to the control group). Given these assumptions, retention rates from past RCTs conducted by the study team within the target population, a two-sided alpha of 0.05 and 80% power, we will enroll a total of 450 participants (225 in each arm) to sufficiently power the trial.

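### Baseline tests decide whether the primary analysis is an unadjusted chi-square or a log-binomial model, and neither names the age and gender strata; one stratum-adjusted analysis should be prespecified

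*Protocol article*

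**What the plan says.** The Statistical analysis section of the protocol article first sets up between-arm tests: "Baseline characteristics will be compared between groups using chi-square tests for binary or categorical outcomes, and Wilcoxon rank-sum tests for continuous outcomes". It then states the primary comparison: the proportion returning a test by the 3-month visit "will be compared across groups using a chi-square test or log-binomial regression if participant characteristics are found to vary at baseline between groups". It gives no threshold for varying and no covariate list.

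The section on randomisation and sample size describes a stratified design: "A stratified randomization technique will be used to ensure equivalent 1:1 allocation of study conditions across three gender groups", crossed with three age groups (14–17, 18–21 and 22–26), which makes 3 × 3 = 9 strata. "Within each age/gender strata, participants will be randomized in blocks of 4". Neither age group nor gender is named in either version of the primary analysis.

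**The concern.** The choice between two primary analyses is left to the observed baseline data. If randomisation was done properly, a baseline difference between arms is a chance event. A test of it says nothing about whether the characteristic predicts screening, so covariates would enter because they happened to differ and not because they matter for the outcome.

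The rule also works against the design. Age group and gender are the two factors that the randomisation forces towards balance, so they are the least likely to be flagged. The default chi-square then leaves out the factors that the investigators chose to stratify on. When those factors predict uptake, the chi-square variance includes between-stratum variation that the design has already removed from the treatment comparison. At stake are a primary analysis that is not fixed in advance and some precision that could be had for nothing.

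**Working it through.** **Planning figure.** The inputs are "a two-sided alpha of 0.05 and 80% power", "we estimate that 20–25% of the control group will complete STI screening" and "relative risk of 1.5 comparing the proportion completing STI screening in the intervention group to the control group". With pooled variance under the null,

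n per arm = [1.96·√(2p̄q̄) + 0.842·√(p₀q₀ + p₁q₁)]² / (p₁ − p₀)².

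For 25% vs 37.5%, p̄ = 0.3125 and n = [1.96·√0.4297 + 0.842·√0.4219]² / 0.125² = 215 per arm. The planned 225 per arm gives 81.8% power before dropout. (At 20% vs 30% the same formula gives 294; that is a separate matter, and this point does not depend on it.) The checks below start from 25% control uptake and 225 per arm.

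**How often the rule switches.** For k independent characteristics and an assumed 5% threshold, P(at least one flagged) = 1 − 0.95^k: 14% (k = 3), 23% (k = 5), 40% (k = 10), 64% (k = 20).

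**Does the switching inflate type I error?** The two-stage rule was simulated with 450 participants, 22.5% uptake, 5 or 10 independent binary characteristics and 8,000 null trials per setting. A linear model with robust variance stood in for log-binomial regression. Type I error was 0.051–0.055 under the rule and 0.052–0.055 for the chi-square alone. The Monte Carlo standard error is √(0.05 × 0.95/8000) ≈ 0.002, so the two do not differ. Reporting whichever analysis was significant, which the protocol does not allow, gave at most 0.058.

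**What omitting the strata does.** Assume 6 equal strata (3 age by 2 gender, taking the third gender group as very small), evenly spaced control rates averaging 25%, RR 1.5 in every stratum and no dropout. Let B be the variance of control rates across strata.

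- Chi-square type I error = 2[1 − Φ(1.96/√r)], with r = 1 − B/(0.25 × 0.75).
- Power = Φ[(0.125 − 1.96√V₀)/√V₁], with V₁ = [(0.1875 − B) + (0.2344 − 2.25B)]/225.
- For the chi-square, V₀ = 2(0.2148)/225. For the stratified test, V₀ = 2(0.2148 − 1.5625B)/225.

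Worked for 5–45% (rates 5, 13, 21, 29, 37, 45%): B = 0.08² × 35/12 = 0.0187 and r = 0.900. Type I error = 2[1 − Φ(2.066)] = 3.9%. √V₁ = 0.0401. Chi-square power = Φ[(0.125 − 1.96 × 0.0437)/0.0401] = 83.7%. Stratified power = Φ[(0.125 − 1.96 × 0.0406)/0.0401] = 87.1%.

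| Control rates across strata | B | r | Chi-square type I error, formula / simulation | Chi-square power, formula / simulation | Stratified power, formula / simulation |
|---|---|---|---|---|---|
| 20–30% | 0.0012 | 0.994 | 4.9% / 5.0% | 81.9% / 81.9% | 82.2% / 82.0% |
| 10–40% | 0.0105 | 0.944 | 4.4% / 4.4% | 82.8% / 82.7% | 84.8% / 84.8% |
| 5–45% | 0.0187 | 0.900 | 3.9% / 4.1% | 83.7% / 83.6% | 87.1% / 87.1% |

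The simulated gain from stratifying is 0.1, 2.1 and 3.5 points.

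**Sensitivity with all nine strata.** A second simulation used permuted blocks of 4 in 9 strata, 22.5% overall control uptake and assumed stratum shares. Chi-square type I error was 0.051 (no spread), 0.046 (13–33%), 0.043 (7–44%) and 0.029 (3–54%), while the stratified test stayed at 0.048–0.052. Power, stratified vs plain, was 0.756 vs 0.757, 0.763 vs 0.757, 0.813 vs 0.777 and 0.863 vs 0.791. The pattern is the same: nothing without spread, about 4 points at a moderate spread, and more only at an extreme one.

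**The case against.** **The rule looks at baseline data, not outcomes.** A reader might infer that the sponsor could choose the more favourable p-value. The text does not support that: the trigger is a baseline comparison, and the simulation shows no material change in type I error. The 40% and 64% are chances of changing the analysis, not of a false positive. They also rest on independent tests and on a threshold that the article does not state. This part of the objection stands.

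**The chi-square does not lose planned power.** A reader might also infer that the trial falls below its planned power because of this test. It does not. Under stratified allocation its power rises slightly with spread (81.8% with none, 83.7% at 5–45%). What is forgone is a further gain. Nor can the chi-square be called conservative without a condition: that holds only if uptake differs by age or gender, and a conservative test does not threaten validity. This stands too.

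**Imbalance can be real after exclusions.** Participants without 3-month data are to be removed. If the baseline comparison is made in that reduced set, differences need not be pure chance. This is fair, but significance tests would still be a poor guide to which covariates predict screening.

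**An article condenses.** The covariate list, a convergence fallback and pooling of sparse strata may sit in a full protocol or SAP that is not shown, so silence on them is no fault. The selection rule is different: it is stated, and supplying those details would leave baseline tests in charge of the model.

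**Conclusion.** The point holds as a fault in a stated rule. The primary analysis is chosen by baseline tests, and the stratification factors are named in neither option and would seldom enter through the rule. The trial's validity is not in question, because the effect of the selection rule on type I error is negligible.

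The precision cost is conditional. It is nil if uptake is similar across age and gender. At assumed stratum control rates of 10–40% or 5–45% it is about 2–4 points of power, with chi-square type I error near 4%. The documents give no uptake by age or gender, so the size is an assumption; the existence of the rule is not. The change is worth making because adjusting for the strata costs essentially nothing when they are not prognostic and helps when they are.

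**What to change.** Replace the conditional sentence with one prespecified primary analysis: the relative risk of kit return by the 3-month visit, with arm, age group and gender group in a log-binomial model, and modified Poisson regression with robust standard errors if that model does not converge. A Mantel-Haenszel relative risk stratified by age and gender group would serve equally well. State in advance a rule for pooling the 'other' gender level, which is likely to be sparse. Report the unadjusted chi-square as supportive. Present baseline characteristics descriptively, and do not use tests of them to choose the test or the covariates.

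The cost is wording only: age and gender are already recorded for every participant at randomisation, and neither the sample size nor the data collection changes.

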### STI treatment

For participants who opt to take the STI testing kit (intervention or control) they can: 1) complete it and return it to a study staff immediately, 2) take the test with them, complete it at a later time and drop it off at the designated study office, or 3) complete it at a later time and coordinate with a study staff to have it picked up at a location they choose.

All participants (intervention and control) who test positive for a STI will receive an assisted referral to a Public Health Nurse at IHS with whom we have partnered on this study to ensure all participants who test positive for one or more STIs receive timely and high-quality treatment.

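### The primary analysis is called intent-to-treat but deletes dropouts without 3-month data, although kit return, as the protocol defines it, can be determined without the 3-month survey

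*Protocol article*

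**What the plan says.** The Statistical analysis section of the protocol article makes three statements that have to be read together.

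- Principle: "Study hypotheses will be tested using an “intent to treat” analysis".
- Primary outcome: the arms are compared on "the proportion of participants completing screening (i.e. returning a test to study staff) by the 3-month study visit".
- Exclusion: "For all analyses, participants who drop-out during the study and don’t provide at least 3-month follow-up data will be removed from the analysis".

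The Intervention and Control condition sections offer the kit to both arms after the personalised messages, which are delivered at the first study visit. The STI treatment section gives three routes of return. The first is to "complete it and return it to a study staff immediately"; the other two are later drop-off at the study office and pick-up by staff.

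The Measures section also lists STI screening uptake among the items collected by the self-report surveys.

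**The concern.** The exclusion rule contradicts the stated principle. Whether a participant stays to 3 months is decided after randomisation, so selecting on it gives up the comparability that randomisation provides. The rule applies to all analyses, and nothing in the article confines it to survey-based outcomes.

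The rule also serves no purpose for this outcome. A participant who hands in a kit on the first day and is then lost is an observed success. One who never hands in a kit is an observed non-completion. Both are deleted.

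Returning a kit and attending at 3 months are both forms of engagement with the study, so a link between them is plausible. The arms receive different content, and study staff are not blinded, so retention could also differ by arm. If both hold, the primary comparison is distorted. If neither holds, observed outcomes are still discarded.

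**Working it through.** **Inputs from the protocol** (Participant randomization and study sample size): "a two-sided alpha of 0.05 and 80% power"; "we estimate that 20–25% of the control group will complete STI screening"; "We anticipate POFG will increase STI screening by at least 50% (i.e. relative risk of 1.5"; "equivalent 1:1 allocation of study conditions"; 450 participants, 225 per arm. Retention is said to have been considered, but no figure is given, so every dropout rate below is an assumption.

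**The plan's own figure.** Per-arm size for two proportions, with p̄ their mean:

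n = [1.96·√(2p̄(1−p̄)) + 0.842·√(p₁(1−p₁)+p₂(1−p₂))]² / (p₂−p₁)²

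- 25% vs 37.5%: [1.96·√0.4297 + 0.842·√0.4219]² / 0.125² gives 215 per arm, 430 in total. Enrolling 225 allows 1 − 215/225 = 4.4% loss.
- 20% vs 30%: 294 per arm, 588 in total, before any loss.

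The 450 cannot be reproduced exactly without the retention rate. Under this formula it leaves little room for loss at the favourable end of the control range and none at the other end.

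**Power with everyone analysed, and with random loss.** Power ≈ Φ[(Δ − 1.96·SE₀)/SE₁], with SE₀ pooled and SE₁ unpooled, at 25% vs 37.5%:

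- 225 per arm: SE₀ = √(0.3125·0.6875·2/225) = 0.0437 and SE₁ = √(0.4219/225) = 0.0433. Then (0.125 − 0.0857)/0.0433 = 0.909, and power is 82%.
- 20% lost at random (180 per arm): (0.125 − 0.0958)/0.0484 = 0.604, and power is 73%. The expected proportions are unchanged, so there is no bias.

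At 20% vs 30% the same steps give 69% and 59%.

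**Bias when loss depends on outcome and arm.** Let p be true uptake, s the dropout among screeners (5% here) and d the dropout among non-screeners. The completer proportion is p(1−s) / [p(1−s) + (1−p)(1−d)].

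*No true effect, 25% in both arms; d = 10% control, 20% intervention:*

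- Control: 0.2375 / (0.2375 + 0.75·0.90) = 0.2375/0.9125 = 0.260
- Intervention: 0.2375 / (0.2375 + 0.75·0.80) = 0.2375/0.8375 = 0.284
- Relative risk 0.284/0.260 = 1.09; two-sided rejection rate about 8% by normal approximation and by simulation

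Exchanging the two dropout rates gives 0.260/0.284 = 0.92, with the same rejection rate.

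*True relative risk 1.5, 25% vs 37.5%; d = 20% control, 10% intervention:*

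- Control: 0.2375/0.8375 = 0.284
- Intervention: 0.35625 / (0.35625 + 0.625·0.90) = 0.35625/0.91875 = 0.388
- Relative risk 1.37
- Expected completers 188 and 207; SE₀ = 0.0476, SE₁ = 0.0472; (0.1042 − 0.0934)/0.0472 = 0.229, and power is 59%

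With all randomised participants analysed, the same trials give relative risks of 1.00 and 1.50, a type I error of about 5% and power of 82%.

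**The case against.** Several points stand against a stronger claim.

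- **Bias is not certain.** A reader might infer that the rule necessarily biases the result. It does not. With equal 15% dropout confined to non-returners, the relative risk stays at 1.00 under the null and at 1.50 under the assumed effect.
- **Some design features favour similar retention.** Participants are blinded, both quizzes take about ten minutes, both arms are offered the kit, and gift cards are described without distinction by arm. Unblinded staff and different content point the other way. The protocol does not settle which prevails.
- **Power need not fall.** If every dropout were a non-returner, nominal power would rise slightly: 85.0% at a 25% control rate with 15% dropout. That would be for the uptake of a selected group, not of those randomised.
- **No kit log is described.** That staff will know who returned a kit is a fair inference from the definition, not a stated fact. Because the surveys also ask about screening uptake, a reader could take the survey as a second source. The Statistical analysis section nevertheless defines the outcome by kit return.
- **Month-6 attenders.** A reader might infer that someone who misses month 3 but attends month 6 is removed. The sentence joins two conditions, dropping out and lacking 3-month data, and a person seen at month 6 has arguably not dropped out. The text is ambiguous, and the point does not rest on it.

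None of this reconciles the exclusion with the stated intent-to-treat principle.

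**Conclusion.** Wrong as written. The section names intent-to-treat and fixes a completer analysis for the primary comparison. Under the kit-return definition, the exclusion deletes participants whose outcome can be determined.

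The illustrations show distortion in both directions under moderate assumed differences in dropout, and a loss of about nine points of power with no bias if 20% are lost at random. These sizes depend on the assumed dropout rates and the 25% control rate. They show what the rule permits, not what will happen in this trial. The conclusion that the outcome can be determined for everyone depends on receipt of a kit by staff being the source of the primary outcome.

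**What to change.** For the primary outcome, replace the exclusion sentence with wording to this effect:

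*All randomised participants are analysed in the arm assigned. The sole source for the primary outcome is receipt of a kit by study staff, not the survey item. Success is a kit received within a fixed number of days from randomisation corresponding to the 3-month window; every other participant counts as not screened, whether or not the 3-month survey was completed.*

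The fixed day count also closes the window for people who have no 3-month visit. Apply the 3-month-data condition only to survey-based outcomes, and report the completer analysis of the primary outcome as a sensitivity analysis.

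The cost is a change of wording. No new data should be needed provided that staff record the date each kit is received; the article does not describe such a record, so this should be confirmed.

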## Discussion

This study protocol has many strengths. First, Protecting Our Future Generation is among the first self-care interventions uniquely focused on sexual health among Native American youth and young adults who endure significant sexual health disparities and are under-represented in sexual health research [15]. Second, this study draws on an unconventional and nuanced approach to sexual health self-care through the use of self-assessments combined with personalized messaging, and self-administered non-clinic based STI screening. These approaches have the potential for widespread uptake within communities served by Indian Health Service, and provide complementary alternatives to provider-driven, clinic-based care [4, 11, 13, 16]. Third, the self-assessment will include a risk prediction/clinical prediction rule to assist with identifying those at greatest risk for STIs, which is urgently needed in this and other settings where STI rates are climbing. Although clinical prediction rules have the capability to minimize resource use and slow the spread of infection, they are infrequently developed and uncommonly used in sexual health care; our study has potential to convert clinical prediction rules into a client-driven tool for improving uptake of sexual health care [15].

Fourth, this research is rooted in Asset Theory, an under-utilized framework for understanding sexual health risk and protective behaviors, and a model which may be particularly suited to Native and other indigenous communities [25]. A focus on assets and resources acknowledges the social/environmental determinants of sexual health and is more congruent with Native American and other indigenous belief systems, as well as a necessary move away from a focus on static, individual traits [26]. Research shows assets and resources can: 1) create future orientation by shaping opportunity structures, 2) stimulate maintenance of existing assets and resources by motivating prudent and protective behavior, 3) provide a foundation for risk-taking, and 4) increase personal efficacy [24, 25]. Despite research showing a predictive relationship between number of assets and resources and protective sexual health practices among youth, our study would be the first to do this within a Native American context [23, 26].

A limitation of this study is that data are collected via self-report and subject to response bias. The study uses tablets and REDcap technology so that surveys can be self-administered in an attempt to minimize this bias. Another limitation is that the intervention involves different components and we won’t necessarily be able to tease apart the impact of each individually (i.e. quiz with clinical risk prediction tool vs. messaging).

If efficacious, POFG may be a model of sexual health self-care for Native American youth and young adults adaptable for use in diverse settings. The use of self-administered sample collection for STI screening, which our study team has proven acceptable and feasible with the participating tribal community, further enhances the ability of Native youth and young adults to take their sexual health into their own hands [28]. The design of POFG, which is tablet-based, brief and confidential, allows for ready implementation through various systems, including: schools, IHS’s Public Health Nursing department, and Tribal Community Health Representatives and Division of Health. To the study team’s knowledge, this is the first rigorous evaluation of a sexual health self-care intervention that incorporates self-administered STI screening for Native American youth and young adults.

